#### Outcome assessment

The outcome assessment entails a *comparative evaluation* comparing the Better@Home cohort with a matched historical control group at GR admission and immediately post-GR, as well as a *follow-up evaluation* assessing the course of all outcomes between GR admission and three months of follow-up, solely in the Better@Home cohort. Table 2 presents the background characteristics, outcomes measured at each time point and the data collection methods for the prospective cohort study.

**Table 2 Tab2:** Background characteristics and outcome measures per time point

	Admission GR		Post GR		Follow-up 3 months
	**BH**	**CU**	**BH**	**CU**	**BH**
Patients					
*Outcome measures*					
Independence in daily functioning (BI)*	EPF	EPF	FI	EPF	FI
Performance in daily functioning (COPM-p)^#^	FI		FI		FI
Satisfaction with performance in daily functioning (COPM-s)	FI		FI		FI
Quality of life (EQ. 5D-5 L)	FI		FI		FI
B*ackground characteristics*					
Age	FI	EPF			
Sex	FI	EPF			
Educational level	FI				
Living arrangement	FI	EPF			
Diagnosis relevant for rehabilitation	RF	EPF			
Frailty (GFI)	FI				
Screening digital skills (Quick scan Pharos)	FI				
Informal caregivers					
*Outcome measure*					
Caregiver burden (CSI)	SQ		SQ		SQ
B*ackground characteristics*					
Age	SQ				
Sex	SQ				
Relationship to the patient	SQ				
Travel distance to the patient	SQ				

*BH* Better@Home cohort, *CU* Historical Control Group (care as usual), *EPF* Electronic Patient File, *FI *Face face-to-face interview patient, *RF* registration form care professionals, *SQ * structured questionnaire primary informal caregiver, *BI * Barthel-index, *COPM-p* Canadian Occupational Performance Measure-performance measure, *COPM-s * Canadian Occupational Performance Measure-satisfaction measure, *Eq. 5D* EuroQol health-related quality of life, *GFI* Groningen Frailty scale, *CSI* Caregiver Strain Index

*) Primary outcome measure comparative evaluation; ^#^) Primary outcome measure follow-up evaluation

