#### Comparative evaluation

 The primary outcome measure for the *comparative evaluation* is independence in activities of daily living, assessed with the Barthel Index (BI) at admission to the GR facility and within two weeks post-GR, after completion of the GR trajectory. For both the Better@Home cohort and historical control group, the BI scores at admission are retrieved from the electronic patient files (EPF). The post-GR scores of the BI for the historical control group are also retrieved from the EPF. This data is routinely gathered by healthcare professionals of the participating GR facilities and stored in the EPF, most commonly in the Clinimetric Measurements tab. However, the post-GR scores of the BI for the Better@Home cohort are assessed by trained research assistants within 2 weeks of discharge. This is due to local GR protocols in which GR facilities do not routinely assess the BI after completion of home-based GR.

The BI, initially described by Mahoney and Barthel, is a 10-item measure of activities of daily living used in clinical practice to assess baseline abilities, quantify functional change after rehabilitation, and inform discharge planning. It comprises ten items: feeding, toilet use, bathing, grooming, dressing, bowel and bladder control, chair transfers, stair climbing, and ambulating [21]. In clinical practice, the patients are rated based on their medical records or direct observation. In a research setting, the patient is questioned during a face-to-face interview. Patients are rated on whether they can perform tasks independently, with assistance, or require assistance. The scoring on the modified version of the BI used in the present study ranges from 0 to 20. Higher scores indicate greater independence [21]. The BI’s structural validity, reliability, and interpretability are sufficient for measuring and interpreting changes in the physical function of geriatric rehabilitation patients [21–23].

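### The post-GR Barthel Index comes from a research interview in Better@Home but from routine staff records in controls, so a systematic rating difference would pass almost fully into the programme effect, and the article plans no check for it

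*Protocol article*

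**What the plan says.** The Comparative evaluation part of Outcome assessment (Protocol article, Data collection) gives the source of each BI score.

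- **Admission, both groups:** "the BI scores at admission are retrieved from the electronic patient files (EPF").
- **Post-GR, controls:** "The post-GR scores of the BI for the historical control group are also retrieved from the EPF". On the origin of the file scores: "This data is routinely gathered by healthcare professionals of the participating GR facilities and stored in the EPF".
- **Post-GR, Better@Home:** "the post-GR scores of the BI for the Better@Home cohort are assessed by trained research assistants within 2 weeks of discharge". The reason given: "This is due to local GR protocols in which GR facilities do not routinely assess the BI after completion of home-based GR".

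Table 2 agrees. Its row "Independence in daily functioning (BI)" shows patient file for both groups at admission. Post-GR it shows face-to-face interview for Better@Home and patient file for controls. At three months it shows interview for Better@Home.

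The same section says that the two modes work differently. For routine care: "In clinical practice, the patients are rated based on their medical records or direct observation". For research: "In a research setting, the patient is questioned during a face-to-face interview".

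Under Data analysis, the BI is modelled with group, time, time-by-group and facility-by-group terms, plus facility, age, sex, living situation and diagnosis. No term represents rating mode. The limitations in the Discussion name sparse control data, selection bias, the lack of randomization, residual confounding and the absence of control data after GR. They do not name outcome measurement.

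**The concern.** A before-after comparison between two groups tolerates an imperfect measure as long as the imperfection is the same in both groups at each time point, because it then cancels. Here it need not cancel. Better@Home patients go from a staff rating to an interview by a researcher. Controls stay with staff ratings throughout.

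If patients questioned after their home-based GR score systematically higher or lower than staff would have scored them, the difference appears as extra or missing recovery due to the programme. It could create an effect or hide one. The same BI difference enters the incremental cost-effectiveness ratio. It also bears on whether outcomes are called comparable, which decides between the cost-minimization approach and the ratio.

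The secondary BI course in the follow-up evaluation has the same break between admission and post-GR.

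**Working it through.** **1. Where the mode changes (Table 2 and Comparative evaluation)**

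| | Admission | Post-GR |
|---|---|---|
| Better@Home | patient file, staff | interview, research assistant |
| Controls | patient file, staff | patient file, staff |

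Let m be the average amount by which the interview score exceeds the staff rating the same patient would have received. Then:

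difference in change = (true change in Better@Home + m) − true change in controls = true difference + m.

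**2. Whether the planned analysis can absorb m**

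- Facility, facility-by-group, age, sex, living situation and diagnosis do not change between admission and post-GR. They cannot pick up a shift that occurs only post-GR in one group.
- Frequency matching uses admission BI, which is file-based in both groups.
- A simulation of the stated model confirms this. It used 120:240 patients, eight facilities, a random patient intercept, no true effect, assumed trajectories of 4 to 10 weeks and 60 runs per shift. Only the mean estimates are used here, because 60 runs are too few for rejection rates.

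| Shift added (BI points) | Estimated effect, time as admission/post | Estimated effect at 7 weeks, time continuous |
|---|---|---|
| 0 | −0.04 | −0.01 |
| 0.5 | 0.49 | 0.46 |
| 1 | 1.01 | 0.93 |
| 2 | 1.91 | 1.80 |

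With continuous time, as planned, about 90% or more of the shift is carried into the effect (0.46/0.5 = 92%, 0.93/1 = 93%, 1.80/2 = 90%).

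**3. The plan's own precision**

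Inputs from Setting and population: two-sided 5%, power 80%, variance inflation factor 2, group sizes 120:120 or 120:240.

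- SE in SD units = √[2 × (1/n1 + 1/n2)].
- 120:240: √[2 × (1/120 + 1/240)] = 0.158. Detectable d = (1.96 + 0.84) × 0.158 = 0.44 (stated 0.45).
- 120:120: √[2 × (2/120)] = 0.183. Detectable d = (1.96 + 0.84) × 0.183 = 0.51 (stated 0.51).

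The stated figures are reproduced. The inflation factor widens the variance but gives no protection against a systematic shift.

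**4. Scenario: false-positive rate with no true effect**

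Rate = P(|Z + m/(SD × SE)| > 1.96). The shift m and the BI standard deviation are assumptions, because the article gives neither.

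| Shift, with SD 4 | 120:240 | 120:120 |
|---|---|---|
| 0.5 points | 12% | 11% |
| 1 point | 35% | 28% |
| 2 points | 89% | 78% |

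Example: 1/(4 × 0.158) = 1.58, giving 35%. With SD 3, 4 or 5, a 1-point shift gives 56%, 35% or 24% at 120:240.

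**5. Dependence on the within-patient correlation**

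The planning SE is for two independent groups, whereas the model compares change. Applying the same inflation factor, the SE for change is the planning SE × √[2(1 − ρ)]. The two agree at ρ = 0.5. The article gives no ρ. For a 1-point shift with SD 4 at 120:240:

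- assumed ρ = 0.3: SE = 0.158 × 1.18 = 0.187, rate 27%
- assumed ρ = 0.7: SE = 0.158 × 0.77 = 0.122, rate 53%

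**6. What a tipping point would look like**

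Suppose the observed effect equals the planned d of 0.45. Significance is lost once the shift exceeds 0.45 − 1.96 × 0.158 = 0.14 SD, which is 0.56 BI points if the SD is 4.

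**The case against.** The article discloses the switch and gives a practical reason. Without the interview there would be no end-of-trajectory BI for Better@Home patients at all. Data collection was planned to run until April 2025, so the mode can no longer be changed. Detailed sensitivity analyses often belong in an analysis plan that is not shown, and the Discussion already asks for caution about causality. All of this is fair. It makes the point one about analysis and reporting, not an undisclosed mistake. It does not remove the problem: a reason for measuring the groups differently is not a correction, and the caution in the Discussion rests on confounding and selection, which matching and adjustment address. Neither touches measurement. The statement that the BI is valid and reliable concerns the instrument and does not say that interview and staff ratings are interchangeable.

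A reader might infer more than the article supports:

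- **That the result is biased in the programme's favour.** Nothing in the article gives the direction or the size.
- **That the percentages are the study's error rate.** They follow from an assumed shift, an assumed SD and a two-group planning SE.
- **That mode and effect coincide exactly.** Time is continuous with varying durations, so the transfer is nearly complete but not total.
- **That this is observation against self-report.** Staff ratings may come from records or observation, so the file side is itself mixed.
- **That a file-only comparison would repair it.** A ward-discharge BI for Better@Home patients, if one is recorded, precedes home-based GR, while controls have finished GR. It would replace a mode difference with a timing difference, probably to the programme's disadvantage.

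**Conclusion.** The concern holds. Rating mode, rater and setting change only for Better@Home post-GR. A systematic shift would enter the time-by-group effect almost one for one, and with it the BI difference in the cost-effectiveness analysis. Nothing in the described matching or model can separate the two, and the article does not name the problem.

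This applies to the whole Better@Home cohort, since no facility is excepted. In the two facilities that use USER, the file score is a converted USER score, so an instrument difference may come on top.

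The structural conclusion needs no assumption beyond the article's own description of the two modes. The magnitude is a scenario: at 120:240 with SD 4, about 12%, 35% or 89% false positives for shifts of 0.5, 1 or 2 points. It depends on an unknown shift, SD and within-patient correlation.

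**What to change.** 1. **Tipping-point analysis.** Pre-specify that the primary BI analysis, and the BI difference used in the incremental cost-effectiveness ratio, are repeated after subtracting a range of shifts from the Better@Home interview scores. A range of −2 to +2 points would do, stated as an assumption. Report the shift at which the conclusion changes.
2. **Follow-up evaluation.** Treat post-GR to three months, with an interview at both, as the like-for-like BI contrast. Mark the admission-to-post-GR change as mixed-mode.
3. **Limitations.** Name the difference in rating mode, rater and timing: the Better@Home score is taken up to two weeks after discharge by study staff.
4. **Ward-discharge BI.** Do not present a file-to-file comparison as a same-mode sensitivity analysis. If such a score exists for Better@Home patients, report it descriptively only. State that it precedes home-based GR and so leaves out the phase under evaluation.

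Items 1 to 3 need analysis and reporting text only, with no new visits, assessors or data. The cost is that the primary conclusion carries a wider sensitivity range.

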#### Follow-up evaluation

 The primary outcome of the *follow-up* evaluation is performance in daily functioning, assessed with the “performance” subscale of the Canadian Occupational Performance Measure (COPM-p). A trained research assistant or care professional performs the COPM interview at admission to the GR facility, within two weeks post-GR after completion of the GR trajectory, and after three months of follow-up [27]. The COPM is a patient-centered, occupation-focused outcome measure that detects changes in perceived daily performance over time. The COPM consists of two subscales: the “performance” subscale (COPM-p) and the “satisfaction” subscale (COPM-s). Through a semi-structured interview, patients prioritize up to five daily activities they consider most important and would like to improve. The patients subsequently rate these activities on a 10-point scale regarding performance (COPM-p) and satisfaction (COPM-s) ranging from 1 to 10. Higher scores indicate a better performance or higher satisfaction. The mean scores for the subscales are obtained by dividing the ratings by the number of prioritized activities. Changes in scores are evaluated by asking the participant to rescore performance and satisfaction on the original prioritized activities. The COPM has excellent test-retest reliability and measures changes in daily activity performance [28–30]. In a systematic review of studies in GR, the COPM showed good content validity, good test-retest reliability, moderate interrater reliability, and moderate responsiveness [31]. A 1.3-point difference between pre- and post-measurement indicates a minimally clinically important difference [29, 31, 32].

We selected the COPM-p as the primary outcome for the *follow-up evaluation* as it fits with the Better@Home program, which focuses on participation in daily life. COPM-p scores are not routinely assessed by GR facilities in The Netherlands and could therefore not be used for the *comparative evaluation*, as this data was unavailable for the historical control group. The following four secondary outcomes are measured: independence in daily functioning (BI), patient satisfaction in performing daily activities (COPM-s) [27], and quality of life (EuroQol-5D-5 L) [33], which focuses on ‘health-related quality of life’ outcomes. The EuroQol-5D-5 L includes five dimensions: mobility, self-care, usual activities, pain or discomfort, and anxiety or depression. Each dimension has five levels, ranging from 1 to 5. A lower score indicates a better perceived quality of life. The fourth secondary outcome, the Caregiver Strain Index (CSI), is assessed among the primary informal caregivers of the patients in the Better@Home cohort [34, 35]. The CSI is a 13-item measure that assesses perceived care burden among informal caregivers. The scoring of the CSI ranges from 0 to 13. A higher score indicates a higher level of perceived strain related to care provision.

#### Cost assessment

The cost assessment entails a *cost-effectiveness analysis*, including data from both the Better@Home cohort and historical control group, and a *cost-analysis*, including data solely from the Better@Home cohort. The cost assessment is conducted from a societal perspective, which includes healthcare costs and patient and family costs. Due to the nature of the study participants (older adults, of whom the large majority are retired), productivity losses are not considered.

#### Comparative evaluation

 In the cost-effectiveness analysis, effects on the independence in daily functioning (BI) and healthcare-, patient & family costs are compared between the Better@Home cohort and historical control group at admission to GR and at post-GR, after completion of the GR-trajectory.

Healthcare costs are divided into costs made during inpatient GR and home-based GR. Healthcare costs during inpatient GR consist of the length of stay in the GR facility and (re)admissions to the hospital. This data can be accurately collected from the EPF in both the Better@Home cohort and historical control group. Healthcare costs during home-based GR consist of consultations with care professionals as well as additional healthcare costs. Consultations with care professionals (i.e., physical therapists, occupational therapists, dietitians, speech therapists, physicians, psychologists, nurses, and others) during home-based GR are registered on registration forms by the care professionals and include treatment volume, treatment time, and travel time. Furthermore, the nature of these consultations (at home, outpatient, or remotely using eHealth) is also registered by the care professionals. Additional healthcare costs during home-based GR are collected in a face-to-face interview with the patient after completion of the GR trajectory and include home care, domestic care, hospital care (both inpatient and outpatient), and general practitioner consultations. No data on healthcare costs during home-based GR was gathered for the historical control group, as this was an exclusion criterion.

Regarding patient and family costs during inpatient GR, the costs of informal care are assessed by multiplying an estimated volume of informal care provided during inpatient GR with a standardized reference price per hour [36, 37] in both cohorts. In addition, patient and family costs during home-based GR consist of the volume of informal care received by the patient, which is assessed during the face-to-face interview with the patient post-GR. Travel expenses are calculated by multiplying the number of visits to a healthcare service with standardized distances and transportation prices, including parking fees. Both standard distances and transportation prices are provided by the manual for cost research and reference prices [36, 37].

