### The Better@Home program

The Better@Home program is developed by the eight GR facilities participating in this study in collaboration with a learning network. The learning network includes project group members from the participating GR facilities (e.g., care professionals, managers, and policymakers), as well as (senior) researchers from the three university networks for the care sector. Moreover, representatives of national healthcare insurers, interest groups for older adult patients and informal caregivers, and other relevant stakeholders are also present in the learning network. The learning network facilitates the exchange of experiences and mutual learning across GR facilities.

A pilot project conducted by one of the eight participating GR facilities resulted in a draft version of the program, which led to the development of the final Better@Home program. The following five core components are present in the Better@Home program (Table 1): (1) Replacing part of inpatient GR by home-based GR; (2) Focusing on participation goals during GR; (3) Using eHealth to support rehabilitation; (4) Promoting patients’ self-management by applying Reablement strategies; and (5) Close collaboration between all relevant care partners involved in the GR trajectory. Each participating GR facility established a working group responsible for developing a site-specific, local Better@Home protocol containing the core components of the Better@Home program. While each of the five core components are mandatory, each GR facility retains the freedom to decide to what extent they implement each component in accordance with their local protocols. Each local Better@Home protocol is conducted by the multidisciplinary GR teams in each facility. In the Netherlands, these teams generally consist of physicians, nurses, physical-, occupational-, and speech therapists, dieticians, psychologists, and often complemented by social workers and nurse practitioners. The Better@Home program was gradually implemented between December 2023 and February 2024 and ended in November 2024.

**Table 1 Tab1:** Core components of the Better@Home program

Core components Better@Home intervention program

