*1) Replacing part of inpatient GR by home-based GR* • Each GR facility strives to reduce the duration of the inpatient GR with an average of 5 to 7 days and to replace this by a period of home-based GR. • The length and intensity of the home-based GR can vary and is tailored to the needs of the patient. • The home-based GR should at least partly consist of therapy provided at the patients’ home and can be supplemented with outpatient therapy at the GR facility and/or remote therapy using eHealth.
*2) Focusing on participation goals during both inpatient GR and home-based GR* • Using the Canadian Occupational Performance Measure (COPM), participation goals are set with the patient within the first two weeks after admission. • The participation goals should be relevant both in the inpatient and home-based phase of the GR trajectory and regularly evaluated until the end of the GR treatment. • The participation goals should be easy to understand and made visible to the patients and their informal caregiver(s).
3)*Using eHealth to support rehabilitation* • Exploring the available eHealth options, such as video calling (e.g., via a tablet equipped with software specifically designed for individuals with little to no digital experiences), rehabilitation apps for home exercises (e.g. Physitrack, and activity monitoring using a wearable sensor to monitor daily movement, all aimed at supporting remote rehabilitation. • Assessing the skills of the patient regarding the available eHealth options and providing support and/or training if needed. • Early introduction and involvement of the patient and the informal caregiver(s) to the eHealth application(s) during the inpatient phase. Aim for continued use of eHealth during the home-based phase of the GR trajectory.
*4) Promoting patients’ self-management by applying Reablement strategies* • Enhancing self-management skills and strategies. • Involving the informal caregiver(s) during the GR trajectory and providing support where necessary. • Assess the patients’ social network and support the patient to activate the network if desired and/or needed. • Providing advice and/or training on the use of aids, devices and home adjustments. • Assess the local or regional social services and organized (leisure) activities and how these could support the patient by participating in meaningful activities in daily life.

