#### *Follow-up evaluation* 

A cost analysis is performed in the *follow-up* evaluation which assesses the course of costs in the Better@Home cohort from GR admission up to three months post-GR. In addition to the costs assessed during inpatient and home-based GR, the healthcare-, family & patient costs made during the three months of follow-up are assessed by a face-to-face interview with the patient. These costs include home care, domestic care, hospital care (inpatient and outpatient), general practitioner consultations, mental healthcare utilization, utilization of allied care professionals, use of assistive devices, and informal care utilization.

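### The cost list for the GR period has no line for eHealth equipment or licences, and assistive devices are costed only after GR, so an intervention cost is left out and the cost course is not like for like on devices

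*Protocol article*

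**What the plan says.** The perspective is set at the start of the Cost assessment section: "The cost assessment is conducted from a societal perspective, which includes healthcare costs and patient and family costs".

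The item lists for the GR period are in the Comparative evaluation subsection of Cost assessment:

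- Inpatient phase: "Healthcare costs during inpatient GR consist of the length of stay in the GR facility and (re)admissions to the hospital".
- Home-based phase: "Healthcare costs during home-based GR consist of consultations with care professionals as well as additional healthcare costs". The additional costs "include home care, domestic care, hospital care (both inpatient and outpatient), and general practitioner consultations".
- eHealth appears once, as a mode of contact: "the nature of these consultations (at home, outpatient, or remotely using eHealth) is also registered by the care professionals".
- Informal care and travel make up the patient and family costs.

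The Follow-up evaluation subsection lists home care, domestic care, hospital care and general practitioner contacts again for the three months after GR, and then "mental healthcare utilization, utilization of allied care professionals, use of assistive devices, and informal care utilization".

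On the programme, the text says: "While each of the five core components are mandatory", and the same sentence lets each facility decide how far it implements each one. Table 1, component 3, gives examples of eHealth, among them "video calling (e.g., via a tablet equipped with software specifically designed for individuals with little to no digital experiences"), rehabilitation apps and a wearable sensor. Component 4 offers advice or training on aids, devices and home adjustments.

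The subsection Both studies values each cost as volume times reference price. The Cost assessment part of Data analysis makes a cost-minimization approach conditional on savings with comparable outcomes, and describes the course of costs over the two measurement periods.

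**The concern.** Equipment and licences for a mandatory component are a cost of delivering the intervention. Under volume times price, an item with no recorded volume and no price enters at zero. Controls with home-based GR are excluded, so eHealth used at home during GR falls essentially on the Better@Home side, and leaving it out flatters the programme on that item. The sign and size of the cost difference matter because they decide whether the analysis becomes a cost-minimization or an ICER. The two sensitivity analyses that are named (complete cases, healthcare perspective) do not touch an uncosted item, and the Discussion does not list it as a limitation.

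The second issue concerns the Better@Home cohort alone. If a category is collected only in the second of two periods, the described course of costs can show a rise, or hide a fall, that comes from the item list and not from patients' use.

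**Working it through.** No figure in the plan rests on this point, so there is none to reproduce. The check sets the item lists side by side and then gives an illustrative range.

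**1. Item lists**

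| Item | GR period | Three months after GR |
|---|---|---|
| Length of stay in GR | named | not applicable |
| GR-team consultations, including remote | named | not applicable |
| Home care, domestic care, hospital care, GP | named | named |
| Informal care | named | named |
| Mental healthcare, allied care | psychologists and therapists counted as GR consultations | named |
| Assistive devices | not named | named |
| eHealth devices, software, licences, sensors | not named | not named |
| Home adjustments | not named | not named |

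Two gaps stand out. eHealth equipment has no line in either period, and assistive devices have a line only in the second.

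**2. Effect of the eHealth gap on incremental cost**

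Let c be the uncounted eHealth cost per Better@Home patient, and u the controls' use of the same item relative to Better@Home, at the same unit price. Neither is in the documents.

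Understatement of incremental cost from this item = c × (1 − u).

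With c assumed at EUR 50-300:

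- u = 0: EUR 50-300
- u = 0.5: EUR 25-150
- u = 1: EUR 0
- u above 1: the sign reverses

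**3. Scale against the inpatient days to be replaced**

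Table 1 gives an aim of 5 to 7 days on average. At an assumed EUR 400-500 per day:

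- low value: 5 × 400 = EUR 2,000
- high value: 7 × 500 = EUR 3,500

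With u = 0:

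- smallest share: 50 / 3,500 = 1.4%
- largest share: 300 / 2,000 = 15%

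With the day price widened to EUR 300-600, the ends become 50 / (7 × 600) = 1.2% and 300 / (5 × 300) = 20%. The denominator is the gross value of an intended reduction in inpatient days. The article claims no saving in euros.

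**4. Whether the net direction can be signed**

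It cannot. Control costing closes at completion of GR, and no home-phase costs exist for controls. Better@Home patients are charged for home care, domestic care, hospital care and GP contacts during home-based GR. That difference pushes incremental cost up, while the eHealth gap pushes it down. The documents give no volumes or prices with which to weigh the two.

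**The case against.** The strongest objection is that this is a condensed article. The verb that opens the list of additional costs can be read as illustrative, and the interview form and cost model are not shown. That carries some weight, but the sentence that defines home-based healthcare costs is closed in form, and the authors do name assistive devices in the period where they collect them. The two lists as printed differ.

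Several further objections stand and limit the point:

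- The tablet, app and sensor are examples of available options and facilities set the extent, so the cost per patient may be small or nil at some sites.
- Staff time in eHealth contacts during home-based GR is already costed through registered consultations. Introduction to eHealth during the stay may be covered by the inpatient day price. Only equipment, software and licences used at home clearly lack a line.
- The difference between periods in mental and allied care is weak, because the GR team's psychologists and therapists are counted during GR.
- The cost course is descriptive and within one cohort.

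A reader might infer that aids and home adjustments are also programme costs missing from the Better@Home side. The documents do not support this. Table 1 promises advice or training, not supply, and control patients may have obtained the same items. They are uncounted in both groups during GR, so their direction is unknown, and adding them to Better@Home alone would create a one-sided bias against the programme.

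A reader might also infer that incremental cost is understated overall. The opposing effect of the control window rules out that conclusion.

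**Conclusion.** The point holds in a limited form. Followed as written, the plan leaves eHealth equipment, software and licences out of a comparison made from a societal perspective, although eHealth is a mandatory component. Other things equal, this lowers the Better@Home incremental cost by c × (1 − u), that is, to the extent that usual care used less eHealth. No net direction of bias in incremental cost follows.

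The size is unknown. The figure of about 1-15% of the value of the replaced inpatient days rests wholly on assumed prices and on no eHealth use among controls.

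Separately, the two-period course of costs is not like for like on assistive devices. Both matters are worth correcting, because the printed item lists feed the rule that selects cost-minimization and the description of costs over time.

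**What to change.** **(a) eHealth.** Add a cost per user (device depreciation and licence, at facility purchase prices), multiplied by eHealth use. Table 3 already plans to record that use on registration forms and in patient interviews. Leave out staff time already registered as consultations, so that it is not counted twice. Report incremental cost with and without this line. Charging it to Better@Home alone corresponds to u = 0 and omitting it to u = 1, so the pair brackets the plausible effect as long as controls did not use more eHealth.

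**(b) Course of costs.** Compare the two periods on the categories measured in both, expressed per week because the periods differ in length. Show categories collected only in follow-up, such as assistive devices, separately.

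**(c) Aids and home adjustments.** Do not add them to one group in the comparison with controls. State as a limitation that they are uncosted in both groups.

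The cost is one price request per facility, a few lines in the cost model and a possibly less favourable cost estimate. Parts (b) and (c) need no new data.
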